## Oversight and monitoring

### Composition of the coordinating center and trial steering committee {5d}

*Principle investigator* takes supervision of the trial and medical responsibility of the participants.

*Data manager* organizes data capture and safeguards quality and data.

*Study coordinator* is responsible for the trial registration and coordinates study visits and annual safety reports.

*Study physician* identifies potential recruits, takes informed consent, and ensures follow-up according to protocol.

There is no trial steering committee or stakeholder and public involvement group.

### Composition of the data monitoring committee, its role and reporting structure {21a}

An independent data monitoring committee (DMC) will review on an ongoing basis accumulating study data to safeguard the interests of the participants. The DMC will assess the benefit/risk profile of the intervention during the study, ensure the validity and integrity of the study, review the overall conduct of the study, and provide recommendations to the Executive Committee (EC) regarding the continued conduct of the study [12].

### Adverse event reporting and harms {22}

All adverse events reported by the participants or observed by the investigators will be recorded. Adverse events will begin to be collected after the participant has provided consent and enrolled in the trial. An adverse event is recorded at any time. When an adverse event occurs, it is recorded immediately. If a participant experiences an adverse event after the informed consent document is signed (entry) but the participant has not started to receive any study intervention, the event will be reported as not related to the study drug [13]. All adverse events occurring after entry into the trial and until the 90th day will be recorded. An adverse event that meets the criteria for a serious adverse event (SAE) between study enrollment and the 90th day will be reported to both the ethics committee of the hospital, and the Ethics Committee of Dongzhimen Hospital, Beijing University of Chinese Medicine as an SAE. A serious adverse event for this trial is any untoward medical occurrence that is believed by the investigators to be causally related to study drug and results in any of the following: after receiving the study drug, the participants need to be hospitalized, need to prolong the length of hospital stay, become disabled, be life threatened or dead, have congenital malformation, and other events. Investigators will evaluate the causal relationship between adverse events and study drugs.

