### Outcomes {12}

The primary outcome is the Modified Rankin Scale (mRS) score.

The secondary outcomes are National Institutes of Health Stroke Scale (NIHSS) score, Activity of Daily Living (ADL) Scale score (Barthel index), coagulation function: prothrombin time (PT), activated partial thromboplastin time (APTT), serum fibrinogen (FIB) concentration, and serum hypersensitive C-reactive protein (hs-CRP).

The safety outcomes are liver function and kidney function: alanine aminotransferase (ALT), aspartate aminotransferase (AST), total bilirubin (TBil), blood urea nitrogen (BUN), serum creatinine (Scr), and urine protein (R-PRO), as well as serum fibrinogen (FIB), occurrence of adverse events (AEs) and serious adverse events (SAEs), and occurrence of bleeding events. Adherence of participants will also be assessed.

The exploratory outcomes include fasting lipid panel: total cholesterol (TC), triglyceride (TG), high-density lipoprotein (HDL), low-density lipoprotein (LDL), and recurrence rate (incidence of ischemic stroke events), occurrence of cardiovascular and cerebrovascular events, and mortality rate. A study schedule and evaluation of outcomes are provided in Table 1.

The five elements of the primary outcome and secondary outcomes are specified in Table 2: the domain, specific measurement, specific metric, method of aggregation, and time point.

**Table 2 Tab2:** Five elements of outcomes

	Domain	Specific measurement	Specific metric	Method of aggregation	Time point
Primary outcome	The Modified Rankin Scale (mRS) score	The Modified Rankin Scale (mRS) score	Change from baseline to 14, 28, 60, 90, and 180 days	Proportional-odds logistic-regression model	Baseline, 14, 28, 60, 90, and 180 days
Secondary outcome	National Institutes of Health Stroke Scale (NIHSS) score	National Institutes of Health Stroke Scale (NIHSS) score	Change from screening period to 14, 28, 60, and 90 days	Repeated-measures analysis model	Screening period, 14, 28, 60, and 90 days
	Activity of Daily Living (ADL) Scale score (Barthel index)	Activity of Daily Living (ADL) Scale score (Barthel index)	Change from baseline to 90 and 180 days	Repeated-measures analysis model	Baseline, 90 and 180 days
	Prothrombin time (PT)	Prothrombin time (PT)	Change from baseline to 14, 28, 60, and 90 days	Repeated-measures analysis model	Baseline, 14, 28, 60, and 90 days

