### Procedure for unblinding if needed {17b}

When a serious adverse event occurs, and it is difficult to judge the relationship between the event with interventions or overdose or serious drug interaction with the combined use of drugs, the investigator could reveal a participant’s allocated intervention in the IWRS.

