## Statistical methods

### Statistical methods for primary and secondary outcomes {20a}

The primary outcome will be analyzed by fitting a proportional-odds logistic-regression model to calculate the common odds ratio as a measure of the likelihood that the treatment group will lead to lower mRS scores than the control group (shift analysis).

For secondary outcomes, categorical variables will be compared with chi-square test or Fisher exact test. Longitudinal continuous variables will be analyzed by fitting a repeated-measures analysis model. Additionally, adverse events, serious adverse events, and laboratory abnormalities will also be compared using the chi-square test or Fisher exact test as appropriate.

All analyses will be performed in the intention-to-treat population using SAS version 9.4 (SAS Institute Inc). *P* values of less than 0.05 will be considered statistical significance, and all tests will be two-sided. No adjustments will be made for multiple comparisons.

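### The SAE definition requires the investigator to believe that the study drug caused the event, so unattributed serious events are left out of SAE reporting and the between-group SAE comparison

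*Protocol article*

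**What the plan says.** Adverse event reporting and harms {22} gives the only SAE definition in the article: "any untoward medical occurrence that is believed by the investigators to be causally related to study drug and results in any of the following". The results listed include hospital admission, and then "need to prolong the length of hospital stay, become disabled, be life threatened or dead, have congenital malformation, and other events"; the list applies to participants who have received study drug.

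The same section sets the reporting rule: "An adverse event that meets the criteria for a serious adverse event (SAE) between study enrollment and the 90th day will be reported" to the local ethics committee and to the lead hospital's ethics committee. For an event after consent but before the first dose, "the event will be reported as not related to the study drug". The section also says that all adverse events up to day 90 are recorded and that investigators assess their causal relation to study drug.

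Outcomes {12} lists among the safety outcomes "occurrence of adverse events (AEs) and serious adverse events (SAEs), and occurrence of bleeding events", and among the exploratory outcomes "recurrence rate (incidence of ischemic stroke events), occurrence of cardiovascular and cerebrovascular events, and mortality rate". Statistical methods {20a} states that "adverse events, serious adverse events, and laboratory abnormalities will also be compared using the chi-square test or Fisher exact test as appropriate". Procedure for unblinding {17b} allows the code to be opened when an SAE has occurred and, among other grounds, "it is difficult to judge the relationship between the event with interventions".

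**The concern.** Seriousness and causality are different attributes of an event. Seriousness is a matter of what happened to the participant, and causality is a judgement about why. The definition merges them, so an event with a serious result is an SAE only if the investigator also holds study drug responsible.

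This matters in this population. Participants have an acute stroke with an NIHSS score above 5 and below 15, and all take aspirin. Many serious events will have a ready explanation other than lumbrokinase, and a careful blinded investigator may reasonably choose it. Randomisation makes such case-by-case judgement unnecessary: if all serious events are counted in both arms, an excess shows whether or not anyone recognised it in a single patient. The definition gives up that protection for the SAE outcome, although safety is part of the trial's stated objective. It also narrows what the ethics committees receive as SAEs while the trial is running.

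**Working it through.** No arithmetic applies, because the article states no SAE rate, attribution rate or power for safety. The check is to follow one event through the text and then to compare the sections.

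**Tracing an event.** Take a participant admitted to hospital on day 40 with pneumonia, which the investigator ascribes to the stroke.
1. Definition in {22}: the result is serious, but the causality condition is not met. It is not an SAE.
2. Reporting rule in {22}: only events that meet the SAE criteria go to the ethics committees as SAEs. This one does not.
3. Analysis in {20a}: SAEs are compared between groups, and no other SAE definition is given. It is not counted there.
4. Monitoring in {23}: monitors check that events agree with the protocol's definition, so monitoring upholds the exclusion.
5. What remains: the event is an adverse event recorded before day 90, and so enters the adverse-event comparison. It is not a bleed, a recurrence, a vascular event or a death, so no separate outcome holds it.

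**The same trace for a vascular event or a death.** Steps 1 to 4 are unchanged if the event is not attributed. Step 5 differs. Table 1 schedules bleeding events from day 14 to day 90, and recurrence, cardiovascular and cerebrovascular events and mortality from day 14 to day 180. None of these has a stated causality condition. The event is absent from the SAE tally but present elsewhere.

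**Internal consistency.**

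| Text | What it presumes | Against the definition in {22} |
|---|---|---|
| {17b}, unblinding | An SAE can exist while its relation to treatment is hard to judge | If belief in causality is part of the definition, that judgement has already been made |
| {22}, SAE window | SAEs are reportable from enrolment | Pre-dose events are unrelated by rule, and the result list applies after study drug, so no pre-dose SAE can exist |
| {22}, causality step | Causality is assessed as a step of its own | For SAEs the step is redundant if causality is built in |

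All three fit a definition based on outcome alone. None fits the definition as written.

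**The case against.** The strongest reply is that the events of most interest are collected anyway. Bleeding is a safety outcome in its own right. Recurrence, vascular events and mortality are outcomes followed to day 180, longer than the SAE window. All adverse events to day 90 are recorded and compared whatever their cause, and an independent data monitoring committee reviews accumulating data. This stands, and it limits the point. A reader might infer that unattributed deaths, haemorrhages and recurrent strokes disappear from the trial; the documents do not support that. But the other outcomes do not restore SAE reporting to the ethics committees, do not correct the SAE comparison, and do not cover serious events outside their scope.

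A reader might also infer from {17b} that SAE status is decided with the arm known. The text does not say so. The code-break there follows an event already called an SAE. Reclassification afterwards is conceivable but is inference. What {17b} does establish is the contradiction shown above.

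A third tempting step is to put a number on lost power, or to say that most serious events are filtered out. The documents give no rates for either. Even the direction is open: if drug-caused events were attributed much more readily than background events, a filtered comparison could be more sensitive, not less.

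The pre-dose inconsistency is minor. Those events stay in the adverse-event record and cannot reflect harm from a drug not yet taken.

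Finally, an article condenses its protocol. That excuses omissions, but here a definition is stated in full and is wrong as stated.

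**Conclusion.** The point holds within limits. As written, {22} makes the investigator's attribution a condition of being an SAE. Unattributed serious events are therefore not reported to the ethics committees as SAEs and do not enter the SAE comparison in {20a}, which depends on individual attribution and not on all-cause counts by randomised arm. The damage is confined to SAE reporting, the SAE tally, and serious events with no separate outcome, such as a non-vascular hospitalisation. The definition also contradicts {17b} and the SAE window within {22}.

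The size cannot be derived, and no power figure should be attached. The conclusion assumes only that sites and analysts apply the definition as it reads. The defect is worth correcting promptly because it affects both a declared safety outcome and oversight during recruitment.

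**What to change.** In {22}, delete from the SAE definition the condition that the investigator believes study drug caused the event, and the clause restricting it to participants who have received study drug. Define an SAE by its outcome alone, from consent onward. Record the investigator's causality judgement as a separate CRF field.

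In {12} and {20a}, make all-cause SAEs the compared safety outcome and show related SAEs separately.

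Reconcile {17b} with {22}, so that both treat relatedness as something assessed after an event has been classed as serious. No change to the grounds for opening the code is proposed.

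The cost is a protocol amendment, CRF guidance to the ten hospitals, more SAE forms, and a re-check of participants already enrolled (46 on 29 November 2021, of 220 planned) for serious events not filed as SAEs. Because all adverse events to day 90 are recorded whatever their cause, that re-check can start from existing records.

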### Frequency and plans for auditing trial conduct {23}

Clinical research monitoring units will carry out regular monitoring. At the start of the trial, the monitors will conduct a tutorial on the electronic case report form. As the trial progresses, they will audit the overall quality and completeness of the data, examine source documents, interview investigators, and confirm that the hospital has complied with the requirements of the protocol. The monitors will verify that all adverse events are documented in the correct format and are consistent with protocol definition. Scheduling monitoring visits will be a function of patient enrollment, site status, and other commitments. They will notify the hospital at least 3 weeks prior to a scheduled visit. If a problem is identified during the visit, the monitor will assist the investigators in resolving the issues.

### Plans for communicating important protocol amendments to relevant parties (e.g., trial participants, ethical committees) {25}

All substantial amendments will be notified to ethical committees. In case amendments concern or affect participants in any way, they are informed about the changes. If needed, additional consent will be requested and registered.

### Dissemination plans {31a}

Results of this research will be disclosed completely in international peer-reviewed journals. Both positive and negative results will be reported.

## Discussion

Acute ischemic stroke most often presents as a minor stroke, and its risk of recurrent ischemic events is high, particularly in the first few days [12]. Aspirin is the only antiplatelet agent with a class 1A recommendation in international guidelines [14–16]. However, 15–25% of patients with a recent ischemic stroke who are being treated with aspirin suffer a new ischemic stroke. This phenomenon is known as aspirin resistance [17]. The failure of aspirin in preventing the recurrence of ischemic stroke is not only related to aspirin resistance, but may also be related to the increase in inflammatory mediators, like fibrinogen, which is a key player in atherogenesis, thrombogenesis, or ischemia distal to atherothrombotic stenoses or occlusions [18]. When the mean plasma concentration of fibrinogen is higher than normal 0.6 g/L, the risk of cardio-cerebral infarction or sudden death is 84%. When plasma fibrinogen is greater than 5 g/L, the risk of thrombosis is 4 times higher than normal. Fibrinogen is an independent risk factor for cardiovascular and cerebrovascular diseases [19]. William et al. studied the association between fibrinogen with recurrent vascular events after stroke. They prospectively recruited patients with acute stroke (*n* = 817) and followed them for up to 4 years for the occurrence of fatal or nonfatal recurrent stroke. They found the adjusted incidence of the outcome cluster recurrent stroke was significantly higher with higher levels of fibrinogen (75th to 25th percentile hazard ratio, 1.45; 95% CI, 1.24–1.72) [20].

Lumbrokinase can dissolve fibrinogen and fibrin [7]. Based on previous trials [9, 21], Lumbrokinase plus aspirin were more effective in reducing recurrence of ischemic stroke than aspirin alone and did not increase major bleeding events. As side effects of bleeding are more widely known with the available antiplatelet agents, like clopidogrel, lumbrokinase may open a new window for antiplatelet therapy with no increase in hemorrhagic events if proved. This will not only benefit patients with ischemic stroke, but also potentially patients with carotid stenosis and coronary artery disease who require the placement of drug eluting stents.

These hypotheses are based on the premise that the findings of the previous trials are true. However, the methodological deficiencies of these trials such as inadequate randomization, no double blinding, no placebo control, and incomplete outcome data might lead to various biases. Because of lacking robust evidence, efficacy of lumbrokinase plus aspirin for AIS remains to be established. A well-designed RCT is the gold standard for evaluating the clinical efficacy and safety of medicine [22]. LUCENT is a rigorously designed RCT to evaluate the efficacy and safety of lumbrokinase plus aspirin for AIS. In this trial, the IWRS and double-blind method will be used to avoid the potential selection and detection biases. Furthermore, in the LUCENT trial, patients will be treated for 90 days, followed by a follow-up period of 90 days. The relatively long follow-up period of 90 days will make it possible to assess the long-term effects of lumbrokinase plus aspirin.

There are also some limitations in this trial. We recruited only patients with mild or moderate ischemic stroke at the time of onset and lack of patients with severe ischemic stroke at the time of onset. Therefore, it is necessary to continue the trial of patients with severe ischemic stroke in future trials.

In this trial, we will be able to explore the potential role of lumbrokinase plus aspirin for reducing recurrence of ischemic stroke. The results of this trial will provide clinicians in China direct data in selecting therapeutic options for AIS and may also potentially open a new window for antiplatelet therapy in the cardiovascular and cerebrovascular medicine fields.

## Trial status

Recruiting started in September 2020. The current protocol is version 2 of 28-12-2019. Currently (29th of November 2021), we have recruited 46 participants. Participant recruitment is estimated to be completed around August 2022.

## Abbreviations

ADL: Activity of daily living
AE: Adverse event
AIS: Acute ischemic stroke
ALT: Alanine aminotransferase
APTT: Activated partial thromboplastin time
AST: Aspartate aminotransferase
BI: Barthel Index
BUN: Blood urea nitrogen
CRF: Case report form
CSS: Chinese Stroke Scale
DMC: Data monitoring committee
ECG: Electrocardiogram
EC: Executive committee
FIB: Fibrinogen
Hb: Hemoglobin
HDL: High-density lipoprotein
hs-CRP: Hypersensitive C-reactive protein
IWRS: Interactive Web Response System
LDL: Low-density lipoprotein
MRI: Magnetic resonance imaging
mRS: Modified Rankin Scale
NIHSS: National Institutes of Health Stroke Scale
OB: Fecal occult blood
PCV: Packed cell volume
PLT: Blood platelet
PO: Per os
PT: Prothrombin time
RBC: Erythrocyte count
RCT: Randomized controlled trial
R-PRO: Urine protein
SAE: Serious adverse event
Scr: Serum creatinine
SOP: Standardized operation process
TBil: Total bilirubin
TC: Total cholesterol
TG: Triglyceride
TIA: Transient ischemic attack
U-BLD: Urine latent blood
U-Ket: Urine ketone bodies
U-LEU: Urine leukocyte
WBC: Leukocyte count
